### Handling missing data

The extent of missing data for the primary outcome should be limited, as it is recorded in the daily visits of the study patients. The data entry must be completed electronically in the data management system before discharge and research nurses should make every effort to collect this. Where these time-critical data are missing, multiple imputation methods may be considered to inform a sensitivity analysis.

### Documentation

All protocol-required information collected during the trial must be entered by the investigator, or designated representative, in the Case Report Form (CRF). A paper-based CRF will be used to collect the data. The investigator, or designated representative, should complete the CRF pages as soon as possible after information is collected, preferably on the day of the study visit. Any outstanding entries must be completed immediately after the final examination. An explanation should be given for all missing data.

The completed CRF must be reviewed and signed by the investigator or by an authorized subinvestigator named in the trial protocol. The CRF data will be transferred to an electronic data management system (REDCap). Completeness, validity and plausibility of data are examined by the management system which thereby generates queries. The investigator or the designated representatives are obliged to clarify or explain the queries. At the end of the trial, the principal investigator will retain the originals of all CRFs. The data will be managed and analyzed in accordance with the appropriate standard operating procedures (SOP).

### Assessment of safety

According to the international principles of the Good Clinical Practice (ICH-GCP) the term “adverse event” covers any clinically relevant sign, symptom, syndrome or illness that appears or worsens in a subject during the period of observation in the clinical trial and that may impair the subject’s wellbeing.

Adverse events fall into the categories nonserious and serious. Nonserious adverse events will not be documented in the VIT study. From the beginning of the study until the regular end of trial at 14 days (±4) follow-up or until premature withdrawal of the patient, all serious adverse events (SAE) must be documented on a “Serious Adverse Event Form” that is available in the Investigator Site File. Any other complications that are considered as clinically relevant by the investigator should be documented in free text.

Serious adverse events must be reported by the attending physician to the principal investigator within 1 day after the SAE becomes known. The principal investigator is responsible for registering all SAEs and for checking incoming SAEs for completeness, correctness and plausibility. In the event of an SAE, the principal investigator will inform the local Ethics Committee without delay. Analysis of safety-related data is performed with respect to frequency of SAE in both treatment groups.

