### Interventions

The patients included will be randomized in a 1:1 ratio either into the VIT group or into the control group in each of the nine injuries separately. Patients of the VIT group will receive a short instruction regarding the use of the already-accredited and CE-certified VIT system. Afterwards, the VIT system will be applied to the foot in the case of a lower extremity fracture or to the hand in the case of an upper extremity injury. The therapy interval of pneumatic compression will be chosen as recommended by the company: 24 h a day in the preoperative period and 6 to 8 h in the postoperative period. In the control group the injured extremity will be splinted and elevated for 24 h a day in the preoperative period. In the postoperative period the time of elevation is recommended according to the soft tissue swelling. In both groups the duration of the therapy (pneumatic compression or elevation) will be documented during the daily study visits. In all patients, no further antiswelling interventions, such as lymphatic drainage, will be applied. The primary investigator will perform an interim analysis regarding the presence of adverse events and dropouts after the inclusion of the first 30 patients. In case of the occurrence of any adverse event related to the study, the responsible local Ethics Committee will be informed to decide whether the study can by continued or not. No forms of nonignorable clustering regarding the primary outcome parameter have been detected during planning of the study.

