### Evaluation

The primary outcome parameter (time to operability) will be assessed day-to-day by one of two independent experienced orthopedic senior consultants, who will define whether the soft tissue permits definite surgical treatment of the fracture, irrespective of other reasons that do not allow surgical treatment. These independent examiners are not involved with the design of the study. The definition of operability is decided by these blinded examiners based on two basic rules: (1) that there is crumpling of the skin at the surgical side and (2) that suturing of the skin without tension will be possible after definitive operative treatment. For the assessment of the primary outcome parameter, the time from injury to the first day of operability will be documented regardless of the time of definitive surgical treatment.

The time schedule of the study and the primary and secondary outcome parameters and respective measurements are shown in Table 1 and Fig. 2. The final follow-up will be obtained 14 (±4) days after the patients have been formally discharged.

**Table 1 Tab1:** Please check if we have captured the tables correctly.Study outcome measures of the Vascular Impulse Technology (VIT) study

Item	Outcome measurement	Measurement point	Primary/secondary outcome parameter
Operability	Time from injury to operability (days)	Daily visit preoperatively	Primary
Soft tissue swelling	Girth measurements of the injured and the uninjured contralateral extremity (cm)	Daily visit pre and postoperatively and 14 days after submission	Secondary
Pain level	Visual Analog Scale (VAS)	Daily visit pre and postoperatively and 14 days after submission	Secondary
Pain medication	Substance and dosage of painkillers	Daily visit pre and postoperatively and 14 days after submission	Secondary
Complications	Detailed description of complications	Daily visit pre and postoperatively and 14 days after submission	Secondary
Revision surgeries	Detailed description of revision surgeries	Daily visit postoperatively and 14 days after submission	Secondary
Duration of total hospital stay	Days	At the day of submission	Secondary

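### The interim safety review and the Ethics Committee trigger cover adverse events of any seriousness, but nonserious related events have no assured record or relatedness judgement

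*Protocol article*

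**What the plan says.** All references are to the protocol article.

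- **Assessment of safety** defines an adverse event as a term that "covers any clinically relevant sign, symptom, syndrome or illness that appears or worsens in a subject during the period of observation", and splits such events into nonserious and serious. It then states: "Nonserious adverse events will not be documented in the VIT study". SAEs go on a dedicated form, reach the principal investigator within 1 day and are passed to the Ethics Committee. The section adds: "Any other complications that are considered as clinically relevant by the investigator should be documented in free text". On analysis it says: "Analysis of safety-related data is performed with respect to frequency of SAE in both treatment groups".
- **Interventions** sets the only interim safety review that the article describes: "The primary investigator will perform an interim analysis regarding the presence of adverse events and dropouts after the inclusion of the first 30 patients". It continues: "In case of the occurrence of any adverse event related to the study, the responsible local Ethics Committee will be informed", so that the committee can decide on continuation.
- **Criteria for termination of the trial** lets the trial end over health hazards shown by how common or how severe adverse events are, again without restriction to serious ones.
- **Evaluation**, Table 1, lists complications as a secondary outcome, measured as "Detailed description of complications" at the daily visits before and after surgery and at the 14-day follow-up.

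**The concern.** Three decision rules (the 30-patient review, the Ethics Committee notification and termination) use a wider set of events than the one the trial undertakes to document and analyse under the name of adverse events. Staff who follow the safety section leave a nonserious event undocumented as an adverse event. Staff who follow the Interventions section need that same event, with a view on whether it is related to the study.

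What is at stake is whether the early review means what it appears to mean. The device is to run 24 h a day before surgery and 6 to 8 h after it. The Background says that there are no studies for the upper extremity or for the tibial head, shaft and pilon, and no data yet for this generation of the device. Patients are told about its potential adverse events at consent. If nonserious related events are recorded unevenly, a quiet review after 30 patients could reassure more than it should, and events not recorded at the time may not be recoverable later.

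**Working it through.** No sample size, power or alpha figure bears on this point, so there is no stated figure to reproduce. The check is a comparison of the sections.

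**Step 1. What each rule needs and what is assured.**

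| Rule | Section | Events it refers to | Assured record |
|---|---|---|---|
| Review after 30 patients | Interventions | Adverse events, any seriousness, plus dropouts | SAEs |
| Ethics Committee informed | Interventions | Any adverse event related to the study | SAEs; no relatedness judgement stated |
| Ethics Committee informed | Assessment of safety | Any SAE | SAEs |
| Termination | Criteria for termination | Frequency or severity of adverse events | SAEs |
| Safety analysis | Assessment of safety | SAEs only | SAEs |

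Only the third and fifth rows match the documentation rule.

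**Step 2. Follow one nonserious event thought to be caused by the device.**

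1. If it is clinically relevant, it is an adverse event by the protocol's own definition.
2. It is not serious, so the safety section excludes it from adverse event documentation.
3. It may still be written down as a complication, under Table 1 or in free text. The free-text route opens only if the investigator considers the event clinically relevant. The Randomization section says that blinding patients and assessors is not feasible, and nothing suggests that this investigator is blinded.
4. No section says that complications are judged for relatedness, although relatedness is what sets off the notification under Interventions.
5. No section says that the 30-patient review draws on the complication entries.
6. The stated safety analysis does not count the event. It could appear only among the secondary outcomes.

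The event may therefore be recorded somewhere, but nothing assures that it reaches the rules that refer to it.

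**Step 3. Consistency within the safety section.** The definition makes clinical relevance part of being an adverse event. A clinically relevant, nonserious complication is then an adverse event that the section both leaves undocumented and asks to have documented in free text. Both sentences cannot be followed literally for that event.

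**Step 4. Scale of the review.** It takes place after 30 of 280 planned patients (30/280 = 10.7%). With 1:1 allocation about 15 of them are on the device (30/2 = 15). This is approximate, because randomization is separate for nine injury types. With so few patients, a handful of unrecorded events could change what the review shows.

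**The case against.** The strongest reply is that the trial does collect these events under another name. Complications are a named secondary outcome, described in detail at every daily visit and at the 14-day follow-up, and Table 1 limits them neither to serious events nor to one group. The free-text line adds other relevant complications. Pain and painkiller use are recorded at the same visits, and patients are told to report exceptional events at once. Under Statistical methods, categorical endpoints are compared by chi-square test, so complications could be compared between groups as a secondary outcome. Read together, the safety section may mean only that nonserious events get no separate adverse event form. The device is also CE-certified, and form layout is often left to the full protocol.

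Much of this stands. A reader might infer that the interim review and the Ethics Committee trigger run on data that the trial does not collect, so that a nonserious device event could never surface. The documents do not support that. SAEs are fully documented, the review also covers dropouts, and many nonserious events would enter as complications. For the same reason, a calculation that sets the chance of detecting such events to zero would be wrong. Nor are the two Ethics Committee statements strictly contradictory, since both can apply.

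The reply does not supply a relatedness judgement, a stated link from complications to the review or the notification, or a way to follow both sentences of the safety section. Nor is this detail left to another document: the article positively states that nonserious events are not documented.

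**Conclusion.** The point holds in limited form. The rules under Interventions and under the termination criteria cover adverse events of any seriousness, while assured documentation and the stated safety analysis cover SAEs only. Nonserious related events are captured at best as complications, partly at an unblinded investigator's discretion and without a stated relatedness judgement. The safety section is also inconsistent with itself.

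The article gives no expected rate of nonserious device events and no way to tell what share would be caught as complications, so the size stays qualitative. The conclusion rests on the sections read as they stand, and on the assumption that no unshown form already links complications to the review with a relatedness judgement. The primary outcome, randomization and sample size are unaffected. This should be corrected before enrolment, but it does not undermine the trial's main comparison.

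**What to change.** 1. Replace the sentence in Assessment of safety that excludes nonserious events. State instead that adverse events judged related to the study treatment, whatever their seriousness, are recorded with the relatedness judgement on a case report form line, in both groups, at the existing daily visits and the 14-day follow-up.
2. Use that dataset together with the SAEs for the 30-patient review, for the notification described under Interventions and for a safety table by treatment group.
3. Reconcile Interventions, Table 1, Assessment of safety and the termination criteria so that each names the same set of events. Say how complications relate to adverse events, and turn the two Ethics Committee notification statements into one consistent rule.

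The cost is one form line at visits that already take place, slightly more data entry and one further table. Trial status says that enrolment is about to start, so the change can be made before any patient's data are affected.

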**Fig. 1 Fig1:**
[figure not shown]
Schematic illustration of the application and the mechanism of the VADOPlex foot-pump system (with kind permission of the Fa. OPED, http://oped-international.com/)

Several studies have shown each of these to be effective in reducing edema faster than simple elevation and immobilization [20, 21]. The use of an impulse foot-pump system has previously been shown to reduce edema by means of measurement of ankle and toe girths [10, 11, 20]. The clinical advantages of these devices have been determined in the treatment of ankle fractures and calcaneal fractures [10, 11, 13, 14, 20]. The hospitalization period and surgical site infections were reduced in the patients who received the impulse foot-pump system compared to the control group with elevation. However, the effectiveness of the impulse foot-pump system has not yet been investigated in detail, as complications such as postoperative skin necrosis and compartment syndrome, and the amount of pain medication required have not been determined. Furthermore, data for the impulse foot-pump system are only available for its use in the treatment of ankle and calcaneal fractures.

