### Randomization

For each of the nine injury types a separate randomization to the two intervention groups (VIT group or control group) will be performed. The randomization numbers will be allocated in balanced blocks with varying size (permuted blocks) in a 1:1 ratio using the web-based software “Randoulette” provided by the Institute of Medical Informatics, Statistics and Documentation of the Medical University of Munich (https://wwwapp.ibe.med.uni-muenchen.de/randoulette/index.jsp). This software allows different randomization methods to be chosen as well as different sets of parameters for the chosen method. To avoid any potential of predicting the group allocation of future patients, the block length is recorded in a separate document that is withheld from the study site.

In addition, persons with the right to randomize with the software described above do not have the right to read or edit the randomization design chosen within the software. The software stores the result of randomization and the patient’s characteristics as well as the name of the person who randomized and the randomization date in a separate file, and only authorized persons can download this file. Patients are randomized on the day of inclusion in the study. Blinding of the patients and the assessors is unfeasible. The investigators will perform the assessment according to trial criteria.

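### Complications short of an SAE reach the data only through an unblinded investigator's judgement of relevance, which conflicts with their role as a secondary outcome at every visit

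*Protocol article*

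**What the plan says.** All of the following is in the protocol article.

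- **Assessment of safety.** SAEs have a mandatory route: "all serious adverse events (SAE) must be documented on a" dedicated form, up to the 14-day follow-up or withdrawal. Below that threshold, "Nonserious adverse events will not be documented in the VIT study". An exception follows: "Any other complications that are considered as clinically relevant by the investigator should be documented in free text". The stated comparison is of SAEs: "Analysis of safety-related data is performed with respect to frequency of SAE in both treatment groups".
- **Evaluation, Table 1.** Complications are a secondary outcome, measured as "Detailed description of complications" at each daily visit before and after surgery and at the 14-day visit.
- **Randomization.** "Blinding of the patients and the assessors is unfeasible", and "The investigators will perform the assessment according to trial criteria".
- **Interventions.** An interim look at adverse events and dropouts follows the first 30 patients. Any study-related adverse event goes to the Ethics Committee, which decides on continuation.
- **Criteria for termination of the trial.** How common or severe adverse events are is one ground for stopping.
- **Background and rationale.** One reason given for the trial is that "complications such as postoperative skin necrosis and compartment syndrome, and the amount of pain medication required have not been determined".
- **Statistical methods.** Categorical endpoints are compared by chi-square test; complications are not named there.

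**The concern.** Below the SAE threshold, an event enters the data only if someone who knows the allocation thinks it matters. The same skin lesion may be judged differently under a pump bladder and in an elevated limb. If so, the arms can differ in what is written down without differing in what happened, or a true difference can be hidden.

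The events exposed to this filter are of interest to the trial. The Background names skin necrosis as an open question, and the Preliminary data section cites wound and skin complications of 11% versus 44% in an earlier randomized trial. Such events are therefore not rare, and those that fall short of an SAE depend on the investigator's discretion. The Discussion acknowledges bias from unblinded examiners for operability and adds an agreement check. It states no safeguard for complications.

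**Working it through.** **1. The rules side by side, for a nonserious complication that is clinically relevant**

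- Assessment of safety defines an adverse event partly by clinical relevance, so this complication is a nonserious adverse event and is not documented.
- The exception in the same section says it should be documented, in free text, if the investigator finds it relevant.
- Table 1 asks for a full description at every visit, with no relevance filter.
- The interim look and the termination criteria refer to adverse events without limiting them to serious ones. They cannot take account of events that were never recorded.

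One can read the first two rules together as meaning no adverse event form but a free-text note. That reading still leaves the filter in place, and it still does not match Table 1 or the two monitoring provisions.

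**2. The plan's own figures**

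No figure is stated for complications. The sample size for the primary outcome reproduces. A 2-day difference, SD of 2 days, two-sided 5% level and 80% power give 16.71 by the exact t test, so 17 per arm. Allowing for dropout, 17 / 0.85 = 20. I use 20 per arm below because it is the size of the largest strata.

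**3. Size of a recording artefact (recording shares are assumed)**

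With the same true rate p in both arms and recorded shares r1 and r2, the apparent difference is p × (r1 − r2).

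- p = 25%, 90% versus 60% recorded: 0.25 × 0.90 = 22.5%; 0.25 × 0.60 = 15.0%; difference 7.5 points, an apparent reduction of one third.
- p = 25%, 90% versus 75% recorded: 22.5% versus 0.25 × 0.75 = 18.75%; difference 3.75 points.
- 90% versus 60% at the two cited rates: 0.11 × 0.30 = 3.3 points; 0.44 × 0.30 = 13.2 points.
- Masking: with 90% recorded in the control arm and 60% in the VIT arm, a true 25% versus 37.5% would both appear as 22.5% (0.25 × 0.90 and 0.375 × 0.60).

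**4. Chance of a falsely significant result**

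Pearson chi-square at 5%, exact enumeration, 20 per arm, equal true rates, all control events recorded, and the share shown recorded in the VIT arm. The rate 27.5% is the midpoint of 11% and 44%.

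| True rate | 100% | 90% | 80% | 70% | 50% |
|---|---|---|---|---|---|
| 11% | 4.2% | 4.2% | 4.3% | 4.7% | 6.4% |
| 27.5% | 5.2% | 5.6% | 7.0% | 9.4% | 18.6% |
| 44% | 4.5% | 5.5% | 8.5% | 13.8% | 32.6% |

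Within one stratum the inflation is modest unless recording differs a great deal. If all 280 patients were pooled (140 per arm), 80% recording would give 9.1% to 32.3% over the same true rates. The article plans only separate analyses, so that is an outer illustration.

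**The case against.** The strongest reply is that the filter covers a remainder. SAEs are mandatory in both arms whatever anyone thinks of their relevance, SAE frequency is the safety comparison actually stated, and revision surgery is a separate secondary outcome. The gravest events, such as pulmonary embolism, would ordinarily go through the SAE route. Table 1 also fixes the visits identically in both arms. All of this stands, and it limits the point to non-SAE complications and to the content and threshold of recording, not its timing.

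The Documentation section requires missing data to be explained and has the data system raise queries. This helps if the case report form has an expected field. It does less for an entry that is conditional on judgement, because nothing is missing when the investigator sees nothing relevant. Item lists and case definitions may exist in the unseen form, and their absence from an article is no fault. They would not undo a rule that the article states.

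A reader might go further and infer any of the following. The documents do not support them.

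- **All complications are recorded only at discretion.** SAEs are not.
- **Earlier studies left complications undetermined altogether.** The Background sentence concerns events such as skin necrosis and compartment syndrome, together with pain medication. The article itself reports wound and skin complications and surgical site infections from earlier work.
- **The planned chi-square tests certainly use the free text.** Statistical methods does not say so.
- **The trial cannot answer its complication question.** No recording difference is documented in either size or direction, and strata of 14 to 40 patients limit that comparison in any case.

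The Evaluation section calls the operability examiners blinded, while the Randomization and Discussion sections say otherwise. That is a separate contradiction about the primary outcome and does not bear on who records complications.

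**Conclusion.** The point holds for complications below the SAE threshold. The stated rule makes their recording depend on an unblinded judgement of relevance. It also conflicts with Table 1, with the interim look and with the termination criteria. A between-arm comparison of these events is open to differential recording.

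The size is unknown. Under the assumed 25% true rate, the artefact is 3.75 to 7.5 points for the two recording patterns shown, and it could favour either arm. These figures rest on assumed recording shares; only the 11% and 44% rates come from the article. The primary outcome and the SAE comparison are not affected by this rule. The matter deserves correction before enrolment, but it does not threaten the trial's main result.

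**What to change.** 1. Reconcile Assessment of safety, Table 1, Interventions and Criteria for termination of the trial, so that they agree on which events below SAE level are recorded and which of them the interim look and the termination decision use.
2. Replace the relevance filter with briefly defined yes/no items and onset dates, completed identically in both arms at each daily visit and at the 14-day visit. Examples are skin necrosis, other local skin lesion, wound infection, compartment syndrome, phlebitis, thrombosis and pulmonary embolism. Keep free text as a supplement.
3. State that these items, not the free text, are used for the between-arm comparison of complications. Keep the mandatory SAE form unchanged.

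The cost is a slightly longer case report form page at visits already planned, and more minor events recorded and reported. The same unblinded staff would complete the items, so definitions and a forced answer reduce the judgement involved but do not remove it. According to Trial status, enrolment was only about to begin. The form could still be changed cheaply at that stage, whereas events not recorded during treatment may not be recoverable later.
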